# Design and rationale of a large, international, prospective cohort study to evaluate the occurrence of malformations and perinatal/neonatal death using insulin detemir in pregnant women with diabetes in comparison with other long-acting insulins

**DOI:** 10.1186/s12884-016-1177-4

**Published:** 2017-01-18

**Keywords:** Diabetes, Pregnancy, Insulin detemir, Cohort study

## Abstract

**Background:**

There are a lack of data regarding the effect of basal insulin analogues on rates of events like congenital malformation and perinatal mortality in diabetic pregnancy.

**Methods:**

The present study is a prospective, non-interventional, multicentre cohort study conducted in seven countries, designed to assess the safety of insulin detemir during pregnancy, and to monitor the health status of resulting infants (exposed in utero) up to 1 year of age. The study population includes women with type 1 or type 2 diabetes, who are pregnant and being treated with insulin. Data will be collected in the context of routine practice. The primary endpoint is the proportion of pregnancies in women treated with insulin detemir, compared with other basal insulin regimens, which do not result in any of the following events: major congenital malformations, perinatal death or neonatal death. A sample size of 3075 pregnancies was calculated to provide an 80% power to detect a difference of 3.5% between groups in the primary endpoint at a 5% level.

**Discussion:**

The study will also examine other important maternal endpoints (e.g., incidences of severe hypoglycaemia and pre-eclampsia) and perinatal outcomes such as overweight neonates, as well as infant outcomes at 1 year of age. It has a fixed recruitment period from 2013 to 2018, enrolling all eligible patients, and is expected to inform future prescribing with basal insulins in diabetic pregnancy.

**Trial registration:**

ClinicalTrials.gov: NCT01892319 (date registered: 27.06.2013).

**Electronic supplementary material:**

The online version of this article (doi:10.1186/s12884-016-1177-4) contains supplementary material, which is available to authorized users.

## Background

Pregnancy in women with diabetes is associated with an increased risk of complications for the mother and the fetus/newborn. The most severe of these include congenital malformations, as well as perinatal and neonatal mortality.

Three recent nationwide population-based studies conducted in Scandinavia have shed light on the risk of such events in pregnancies among women with type 1 diabetes (T1D) [1–3]. Odds ratios (ORs) of stillbirth (ORs: 3.3 in one study and 3.6 in another), perinatal mortality (ORs: 3.3 in one study and 2.9 in another) and infant death in the first year of life (OR: 1.9) were all shown to be significantly higher among T1D than non-T1D pregnancies [1, 3]. Odds ratios of congenital abnormalities were also significantly elevated (ORs: 2.5 in one study and 2.1 in another) [1, 2].

Furthermore, in a prospective Danish multicentre study of >1000 T1D pregnancies, the perinatal annual mortality rate was 3.1% in women with T1D compared with 0.75% in the background population (OR: 4.1), and the annual rate of congenital malformation was 5.0%, compared with 2.8% in the background population (OR: 1.7) [4]. In this study, serious adverse outcomes (perinatal death and/or congenital malformations) were associated with higher glycated haemoglobin (HbA_1c_) levels before and during pregnancy [4]. Furthermore, even small elevations in HbA_1c_ in pregnant women with diabetes have been associated with significantly increased rates of congenital malformations [5]. Hence, normoglycaemia should be the target in pregnant women with diabetes and in those planning pregnancy. To achieve this, insulin will be required in all T1D patients, and in many type 2 diabetes (T2D) patients. A literature review revealed that available data on the use of basal insulins (including long-acting insulin analogues and neutral protamine Hagedorn [NPH] insulin) in pregnant women with diabetes come largely from retrospective studies [6]. These data suggest that basal insulins can be effective and safe in women with T1D during pregnancy. In a recent retrospective analysis of 113 T1D pregnancies in which women used insulin detemir (IDet) or insulin glargine (IGlar), glycaemic control and pregnancy outcomes were comparable between the two groups with regard to congenital malformations, as well as perinatal and neonatal mortality. There were no perinatal deaths and two offspring (2%, one in each group) were born with a major congenital malformation [7].

However, there are relatively few prospective data on insulin use in pregnancy. Only one randomised controlled trial (RCT) has been performed investigating the use of a basal insulin analogue: a trial comparing IDet with NPH insulin, both in combination with insulin aspart, in pregnant women with T1D [8]. In this study, IDet resulted in significantly lower fasting plasma glucose (FPG) in pregnancy compared with NPH insulin, with similar HbA_1c_ levels and rates of hypoglycaemia [8]. This trial also suggested that both insulins were well tolerated with regard to perinatal outcomes [9].

While these data are valuable, RCTs are not the best method for evaluating the occurrence of rare events like congenital malformations and perinatal/neonatal mortality. Population reports have reported outcome incidences, but not in relation to specific treatments [10–13]. Instead, large observational studies are required to assess safety and to attempt to detect this type of event, hence, such a study is warranted.

In addition to this clinical need, the European Medicines Agency (EMA) has requested that a post-authorisation safety study (PASS) be performed to monitor the long-term safety of IDet in pregnant women, covering both gestation and lactation.

The present study was therefore initiated to evaluate the safety of IDet in pregnant women, with a focus on the occurrence of malformations and perinatal/neonatal death. It will also examine other important maternal endpoints (e.g., incidences of hypoglycaemia and pre-eclampsia) and perinatal outcomes (e.g., incidences of overweight neonates/large for gestational age [LGA]), as well as infant outcomes at 1 year of age.

## Methods/design

This study is an international, prospective, non-interventional, multicentre cohort study to monitor and assess the safety of IDet in comparison with other types of insulin treatment during pregnancy, and to monitor the health status of the resulting infants (who were exposed in utero) at 1 month and 1 year of age. The large-scale data collection undertaken in this study will allow comparison and analysis of the occurrence of events between the various insulin treatment regimens. The same parameters will also be monitored for other injectable antidiabetic treatment regimens used during pregnancy.

The study is non-interventional. The assignment of patients to a particular therapeutic strategy is not decided in advance by a trial protocol but instead falls within current practice. Data will be collected in the context of routine practice, with very few exclusion criteria, and hence the results are expected to be more broadly applicable to the real-world population than those of typical RCTs.

The primary objective is to estimate the proportion of pregnancies in women treated with IDet, compared with other basal insulin regimens, which do not result in any of the following events: major congenital malformations, perinatal death or neonatal death (assessed at up to 4 weeks after delivery). The definitions of these and other key terms, within the context of this trial, are provided in Table 1.

**Table 1 Tab1:** Definitions of key terms

Term	Definition
Congenital malformation	A morphological defect of an organ, part of an organ or larger region of the body resulting from an intrinsically abnormal developmental process
Foetal macrosomia	Birth weight above 4 kg
Large for gestational age	Live born infant with birth weight >90th percentile for gestational age and sex according to local reference
Major malformation	A life-threatening structural anomaly or an abnormality likely to cause significant impairment of health or functional capacity and which needs medical or surgical treatment; examples are abnormalities likely to lead to serious handicap or likely to lead to major cosmetic defects (e.g., cleft lip) and which may require major surgery to repair (e.g., atrial septal defect or ventricular septal defect)
Major hypoglycaemia	A hypoglycaemic episode in which the patient is not able to treat themselves and in which oral carbohydrates, glucagon or intravenous glucose has to be administered to the patient by another person because of severe central nervous system dysfunction
Neonatal death	Death of an infant between 7 and 28 completed days after delivery
Perinatal death	Death of a foetus/infant at ≥22 completed gestational weeks and <1 completed week after delivery
Preterm delivery	Delivery before 37 completed gestational weeks
Pre-eclampsia	A condition in pregnancy characterised by new onset of abrupt hypertension (≥140/90 mmHg documented on two occasions, ≥6 h and ≤7 days apart) and proteinuria/albuminuria
Spontaneous abortion	A naturally occurring termination of a pregnancy before 22 completed gestation weeks

The study has a fixed recruitment period of 5 years (September 2013 to September 2018), and will include gestation and follow-up of infants at 1 month and 1 year of age. The planned enrolment is 3055 patients.

The study population will include women with T1D or T2D (as assessed from maternal medical history) who are pregnant and being treated with insulin or other injectable antidiabetic treatment regimens, and who have not changed their basal insulin or other injectable antidiabetic treatment for 4 weeks prior to and following conception. Inclusion and exclusion criteria are listed in Table 2.

**Table 2 Tab2:** Inclusion and exclusion criteria

Inclusion criteria
• Woman with a positive pregnancy test
• Type 1 diabetes or type 2 diabetes, diagnosed prior to conception
• Treated with unchanged basal insulin or other injectable antidiabetic treatment (for those not treated with basal insulin) for 4 weeks prior to and following conception
• Informed consent obtained before any data collection
Exclusion criteria
• Women who have been pregnant for >12 weeks at baseline visit confirmed by ultrasound

### Study endpoints

The primary endpoint is the proportion of pregnancies in women treated with IDet, compared with other basal insulin regimens, which do not result in any of the following events: major congenital malformations, perinatal death or neonatal death (assessed at up to 4 weeks after delivery).

Key secondary endpoints relate to outcomes with IDet versus other basal insulin regimens for the mother, the fetus and the infant at 1 year of age. Maternal endpoints include the incidence of major hypoglycaemia during pregnancy, the proportion of pregnancies complicated by pre-eclampsia and metabolic control (measured as HbA_1c_). Perinatal outcome endpoints include the proportion resulting in fetal macrosomia, LGA, preterm delivery or spontaneous abortion. Infant endpoints assessed at 1 year of age include height, weight, the proportion with diabetes, and the proportion with changes (progression/regression) of major congenital malformations.

Safety data will also be collected in the pregnant women participating in the study, as well as in their offspring up to 1 year of age.

For analyses of the primary and secondary endpoints, only women treated with basal insulin will be included. However, information on all insulins and other injectable antidiabetic treatment regimens will be collected to facilitate comparison and analysis of outcomes in IDet-treated patients versus, for example, patients treated with an insulin pump.

Any change in basal insulin after the baseline visit will lead to exclusion from the statistical analyses of the primary and secondary endpoints, but not from the study. However, changes in dosage or dose interval, or add-on/removal of bolus insulin, oral antidiabetic drugs and/or glucagon-like peptide-1 (GLP-1) agonists, will not lead to exclusion from the analyses.

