### Treatment protocol and follow-up procedures

The frequency of visits will be determined by the individual study sites, and the data will be gathered as part of standard local routine. Only data collection at 1 month and at 1 year follow-up will be performed separately for the purpose of the study.

Data will be collected at various time points, including baseline (occurring as soon as the woman has discovered her pregnancy through a positive pregnancy test), standard routine visits throughout pregnancy, delivery (relating both to the mother and the neonate), 1-month follow-up and end of study (1-year follow-up) (Fig. 1). Postpartum follow-up at 1 month and 1 year will be performed using questionnaires (see Additional files 1 and 2) and telephone interviews. The 1-month follow-up will collect information on height, weight, neonatal death (yes or no), congenital malformations not detected at delivery, duration of exclusive/partial lactation and any adverse events (AEs) relating to the neonate. The 1-year follow-up will collect information on the duration of exclusive and any lactation, height, weight, diabetes in the infant (yes or no), changes in major congenital malformations and any AEs relating to the infant.

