### Statistical considerations

The analysis set will consist of all pregnancies among patients who are treated with basal insulin and have not changed basal insulin product for 4 weeks prior to conception and during pregnancy. Continuous variables will be summarised with descriptive statistics, and categorical variables will be displayed in frequency tables.

The primary endpoint will be analysed using a logistic regression model that will include treatment group, study site, race, hypertension, major hypoglycaemic events during pregnancy, folic acid intake and use of GLP-1 agonists during pregnancy as factors. HbA_1c_ at the start of pregnancy, the end of the first trimester and the end of the second trimester, age and body mass index at baseline, duration of diabetes, blood pressure and previous perinatal complications will be included as covariates. The primary endpoint will be computed for the IDet group and for the ‘other basal insulin’ group and the absolute difference between these proportions calculated, along with the 95% CI and the *p*-value using Fisher’s exact test.

For infant endpoints at 1 year, the proportions will also be analysed using logistic regression. Factors and covariates will be as per the primary endpoint. Analyses regarding height and weight will also be adjusted for exclusive and/or partial lactation period. Similar analyses will be performed for all other endpoints that are proportions.

Means of the continuous endpoints will be compared between the two groups using an analysis of covariance model.

The incidence of major hypoglycaemia during pregnancy will be computed for both treatment groups.

Observations of possible clinical importance (such as the primary endpoint split out according to diabetes type, insulin analogue or use of an insulin pump) will be presented using descriptive statistics.

All statistical analyses will be performed using appropriate statistical software, and tests will be performed as two-sided tests with a significance level of 0.05.

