## Discussion

Outside of pregnancy, long-acting insulin analogues improve glycaemic control, and are associated with lower rates of hypoglycaemia than human insulins [14, 15]. Among the insulin analogues, the European Union labels for both IDet and IGlar allow for consideration of use in pregnancy [16, 17]. In the case of IGlar, this is based on postmarketing data; for IDet, an RCT has been performed, demonstrating significantly lower FPG and non-inferior HbA_1c_ in late pregnancy and similar rates of hypoglycaemia compared with NPH insulin [7].

However, none of these studies were sufficiently large to accurately evaluate the incidence of events such as congenital malformations and perinatal/neonatal mortality in patients receiving insulin during pregnancy. Hence, this long-term, prospective, epidemiological study was initiated-the first of its kind in pregnant women with diabetes.

Although the primary endpoint is based around the incidence of malformation and mortality, the study will also examine a number of other important endpoints. For example, data on incidences of pre-eclampsia, fetal macrosomia and LGA will be collected. Each of these has been shown to occur more frequently in T1D than control pregnancies. Indeed, in a Swedish population study, odds ratios were 4.5 for pre-eclampsia and 11.4 for LGA [1].

Data on the incidence of maternal hypoglycaemia will also be examined in the present study, and compared between different insulin treatments. Severe hypoglycaemic episodes are common in diabetic pregnancy, particularly in the first trimester, and are associated with a variety of factors, including impaired hypoglycaemia awareness, long duration of diabetes, fluctuating plasma glucose values and excessive use of supplementary insulin injections between meals [18].

Furthermore, the study will also examine the health of the infant at 1 year of age, including the proportion with progression or regression of major congenital malformations, as well as early growth (height and weight) and breastfeeding history. Data on such outcomes are currently lacking, and so this trial is expected to fill an important gap in understanding.

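### The 1-year malformation endpoint counts progression and regression as the same event, so a difference between the insulin groups has no direction

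*Protocol article*

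**What the plan says.** The Study endpoints section of the protocol article gives, among the infant endpoints at 1 year, "the proportion with changes (progression/regression) of major congenital malformations". The Discussion restates it, again as one proportion: "including the proportion with progression or regression of major congenital malformations".

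The Treatment protocol and follow-up procedures section summarises the last items of the 1-year data collection as "diabetes in the infant (yes or no), changes in major congenital malformations and any AEs relating to the infant". It refers to questionnaires in additional files, which are not shown.

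On analysis, the Statistical considerations section states: "For infant endpoints at 1 year, the proportions will also be analysed using logistic regression". Factors and covariates are those of the primary endpoint model, and treatment group is one of them. The same section adds that "tests will be performed as two-sided tests with a significance level of 0.05". It does not divide the malformation endpoint by direction.

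**The concern.** Progression is an unfavourable course and regression a favourable one. If either makes an infant an event, the odds ratio for treatment does not say which group fared better. Two problems follow. A pooled difference cannot be read as harm or benefit, and a true excess of progression in one group can be hidden by an excess of regression in the other.

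This matters because the study is a post-authorisation safety study requested by a regulator, and the Discussion presents the 1-year outcomes, this one included, as filling a gap in knowledge. Table 1 also defines a major malformation partly by its need for medical or surgical treatment. If successful repair were recorded as regression, improvement could make up most of the changes and mask progression. That last step is an inference, because the article does not define regression.

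**Working it through.** The article gives no rate, power or sample size for this endpoint, so there is no figure to reproduce. The check covers the wording, the size of the subset, and what pooling can conceal.

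**1. Wording.** Study endpoints and the Discussion both use the singular, one proportion covering both directions. Statistical considerations sends 1-year infant proportions to a logistic model, which needs a yes/no outcome. Read together, the outcome is change (either direction) versus no change.

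**2. Size of the subset.** Inputs from Determination of sample size: 1833 assessable pregnancies, 4.5% major malformations, and a 1:2 split (insulin detemir : other basal insulin). One infant per pregnancy is assumed.

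- Total: 1833 × 0.045 = 82.5
- Insulin detemir: 82.5 / 3 = 27.5
- Other basal insulin: 82.5 × 2/3 = 55.0

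That is about 82 infants, about 27 versus 55. It is an upper-end figure at this rate, because it still includes malformed cases dead by day 28 and those lost between 1 month and 1 year.

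**3. Cancellation.** The counts below are assumed and chosen to show the mechanism. They are not a forecast. The p-values are from Fisher's exact test, unadjusted.

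| Outcome | Insulin detemir | Other basal insulin | Odds ratio | p |
|---|---|---|---|---|
| Any change | 11/27 (40.7%) | 22/55 (40.0%) | (11/16)/(22/33) = 1.03 | 1.00 |
| Progression | 8/27 (29.6%) | 6/55 (10.9%) | (8/19)/(6/49) = 3.44 | 0.058 |
| Regression | 3/27 (11.1%) | 16/55 (29.1%) | (3/24)/(16/39) = 0.30 | 0.096 |

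The pooled endpoint shows no difference, while progression differs by 29.6 − 10.9 = 18.7 percentage points.

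**4. Loss of direction.** Take the same pooled result, 11/27 versus 22/55. If each changed infant is classed in one direction only, progression could be anything from 0/27 to 11/27 in one group and from 0/55 to 22/55 in the other. The difference in progression that fits the pooled result therefore runs from 0 − 40.0 = −40.0 to 40.7 − 0 = +40.7 percentage points. The pooled figure alone does not fix even its sign.

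**The case against.** The strongest reply is that the article names both directions each time it defines the endpoint, so the slash may be shorthand for two categories to be reported separately. The analysis section does not mention this endpoint by name, and nothing prevents a table by direction. The 1-year questionnaire is not shown and may already record direction. This is a possible reading, and it means that the defect is in the stated endpoint and not necessarily in the data. It does not rescue the wording. The Discussion's singular proportion and the binary model both point to one pooled outcome, and if two were meant the text should say so.

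It is also fair that the mirror-image counts were picked to cancel, and that even in so extreme an example neither separate comparison reaches 0.05. Splitting makes the result interpretable but does not make so small a comparison conclusive.

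A reader might go further and infer that infants who die after day 28 are left out of the endpoint, so that a group with more late deaths looks no worse. It is true that the 1-month list has a death item ("neonatal death (yes or no), congenital malformations not detected at delivery"), that Table 1 defines neonatal death as "Death of an infant between 7 and 28 completed days after delivery", and that the summary of the 1-year contact names no death item. But no rule in the article excludes these infants or treats them as missing. The 1-year contact collects any infant adverse events, and safety data are collected in the women "as well as in their offspring up to 1 year of age", so a late death can be captured. How deaths and the denominator are handled is detail that an article commonly leaves to the full protocol or analysis plan. The stronger reading is not supported.

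**Conclusion.** The point holds for the pooling of directions. As written, one secondary safety endpoint treats worsening and improvement as the same event, and its comparison between insulin detemir and other basal insulins cannot be read as benefit or harm.

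The size of the problem cannot be estimated from the article, which gives no rates of progression or regression. The 18.7-point hidden difference rests wholly on assumed counts. The ceiling of about 82 infants rests on the article's own 4.5%, 1833 pregnancies and 1:2 split, with one infant per pregnancy.

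The consequence is limited to this endpoint. The primary endpoint, its analysis and the sample size do not depend on it. The change is worth making because it is cheap and because an imprecise estimate with a direction can be interpreted, whereas the pooled one cannot.

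**What to change.** Replace the pooled endpoint with two, reported and analysed separately among infants with a major malformation:

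- the proportion with progression at 1 year;
- the proportion with regression at 1 year.

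Take direction from the 1-year follow-up, and confirm that the questionnaire records it. Report deaths between day 28 and 1 year among these infants alongside, as their own count, from the infant adverse event and safety data. Counting every such death as progression is a debatable alternative, since a death need not be related to the malformation. A separate count avoids that judgement.

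Make the same change of wording in Study endpoints and the Discussion. The cost is a rewording and, if the form does not yet capture it, an item for direction. The statistical price is fewer events in each proportion. With at most about 27 versus 55 infants, the results should be presented as mainly descriptive.

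### The primary model adjusts for GLP-1 agonist use but not for bolus insulin, oral antidiabetic drugs or diabetes type, so residual confounding by accompanying treatment is possible

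*Protocol article*

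**What the plan says.** The Methods/design section describes a non-interventional cohort: "The assignment of patients to a particular therapeutic strategy is not decided in advance by a trial protocol". Table 2 admits both kinds of diabetes ("Type 1 diabetes or type 2 diabetes, diagnosed prior to conception") and requires basal insulin, or another injectable for women not on basal insulin, to be unchanged for 4 weeks either side of conception. It sets no condition on bolus insulin or oral drugs.

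Under Study endpoints, a change of basal insulin after the baseline visit removes a woman from the primary and secondary analyses. For the accompanying treatments the rule is different: "add-on/removal of bolus insulin, oral antidiabetic drugs and/or glucagon-like peptide-1 (GLP-1) agonists, will not lead to exclusion from the analyses".

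Under Statistical considerations, the primary logistic model has "treatment group, study site, race, hypertension, major hypoglycaemic events during pregnancy, folic acid intake and use of GLP-1 agonists during pregnancy as factors". The covariates are HbA1c "at the start of pregnancy, the end of the first trimester and the end of the second trimester", and "age and body mass index at baseline, duration of diabetes, blood pressure and previous perinatal complications will be included as covariates". The infant proportions at 1 year use the same terms, and the remaining proportion endpoints are to be analysed similarly. Diabetes type, insulin analogue and pump use are named only as descriptive splits of the primary endpoint. A crude difference in proportions with Fisher's exact test is also planned.

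**The concern.** In a non-randomised comparison, the covariate list is the main protection against confounding. This list is specific, down to folic acid and three HbA1c time points, so what it leaves out is a stated choice and not a detail deferred to an analysis plan. Including GLP-1 use accepts that antidiabetic co-treatment can matter. The article gives no reason for including one of the three named co-treatments and leaving out the other two.

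Basal insulin and the rest of the regimen are chosen together in routine care. Women with type 1 and type 2 diabetes are pooled, and type plausibly determines much of who takes an oral drug or uses no bolus insulin. If the detemir and comparator groups differ in these respects at conception, and if the co-treatment or the diabetes type affects outcome beyond the terms already in the model, part of that effect would be attributed to the basal insulin. The shared covariate list would carry the same problem into the other proportion endpoints, such as pre-eclampsia, large for gestational age and preterm delivery. The crude Fisher comparison cannot correct it.

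**Working it through.** **1. Named treatments against model terms**

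| Item | Where the article names it | In the primary model? |
|---|---|---|
| GLP-1 agonist | Study endpoints, change does not exclude | Yes, use during pregnancy |
| Bolus insulin | Study endpoints, change does not exclude | No |
| Oral antidiabetic drugs | Study endpoints, change does not exclude | No |
| Diabetes type | Table 2, both types eligible | No, descriptive split only |

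The omission can be read directly from the text.

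**2. The plan's own figures**

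Event rate (Determination of sample size): 1 − (1 − 0.045)(1 − 0.030)(1 − 0.009) = 1 − 0.955 × 0.970 × 0.991 = 0.0820, which matches the stated 8.2%.

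Sample size: for 91.8% against 95.3%, split 1:2 with 91.8% in the larger group, two-sided 5% and 80% power, the pooled-variance formula gives 1195 + 598 = 1793. That is 2.2% below the stated 1833, close enough to use 1833 (611 and 1222) below. The sample size is not in dispute here.

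**3. Illustration of possible bias (assumed inputs)**

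The documents give neither co-treatment use by basal group nor any effect of co-treatment on outcome. Assume:
- no true basal insulin effect and an overall event rate of 8.2%;
- a co-treatment used by a proportion *a* of the 611 and *b* of the 1222;
- its own risk ratio RR, and no correlation with any model covariate.

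Mean use is p = (a + 2b)/3, the risk without the co-treatment is r0 = 0.082 / [1 + p(RR − 1)], and the false difference is r0 × (RR − 1) × (b − a).

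Worked case, RR 2.0 and 15% v 45%: p = (0.15 + 0.90)/3 = 0.35; r0 = 0.082/1.35 = 0.0607; difference = 0.0607 × 1.0 × 0.30 = 0.0182.

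False difference in percentage points:

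| RR | 25% v 35% | 20% v 40% | 15% v 45% |
|---|---|---|---|
| 1.2 | 0.15 | 0.31 | 0.46 |
| 1.5 | 0.35 | 0.70 | 1.05 |
| 2.0 | 0.62 | 1.23 | 1.82 |

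As shares of the 3.5-point target these run from 0.15/3.5 = 4% to 1.82/3.5 = 52%. Swapping the groups reverses the sign and leaves the sizes similar; the largest becomes (0.082/1.25) × 1.0 × 0.30 = 1.97 points.

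**4. Effect on the 5% error rate**

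SE = √[0.082 × 0.918 × (1/611 + 1/1222)] = 0.0136. The two-sided rejection probability under a false difference δ is Φ(−1.96 + δ/SE) + Φ(−1.96 − δ/SE). For δ = 0.5, 1.0 and 1.5 points this is about 6.6%, 11% and 20%. The SE is that of a crude comparison, so these values are approximate for the adjusted model.

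**5. Room in the model**

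Expected events: 1833 × 0.082 = 150. If site enters as a fixed factor with about 53 levels, it takes 52 parameters. Counting race and blood pressure as one parameter each, the other terms number 14 (treatment, race, hypertension, hypoglycaemia, folic acid, GLP-1, three HbA1c values, age, BMI, duration, blood pressure, previous complications). That is 150/66 = 2.3 events per parameter. Adding oral drugs (1), bolus insulin (2) and diabetes type (1) gives 150/70 = 2.1. Site accounts for most of the load; the additions change the ratio little.

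**The case against.** The strongest reply has five parts.

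- **The quoted sentence concerns changes.** It says that adding or removing co-treatment does not exclude a woman. It says nothing about treatment at conception and is not a licence for unrestricted use. Changes after baseline follow the basal exposure and may lie on the causal path, so adjusting for them could itself bias the estimate. This stands, and it limits the point to status at conception or baseline. It also counts against a GLP-1 term defined over the whole pregnancy.
- **No confounding has been shown.** A reader might infer that the comparison is confounded. That requires both an imbalance between the groups and an effect beyond the model terms, and no section supplies either. Only the possibility is supported.
- **Existing terms absorb part of any difference.** Site takes up prescribing differences between sites. BMI, age and diabetes duration plausibly carry part of the contrast between types, and HbA1c carries the part acting through glucose. This is a fair reason to expect a smaller bias than the table shows, but it does not show that the bias is gone. Within a site, regimen can still vary with basal insulin.
- **Recording of oral drugs.** A reader might infer that oral drugs go unrecorded, because the article says "information on all insulins and other injectable antidiabetic treatment regimens will be collected" and does not name them. That sentence comes from a condensed article and explains why non-basal regimens are captured; it does not list form items. Nor does the plan treat detemir as given alone: the contrast is with other basal regimens, and co-treatment is possible in both groups.
- **The model is already crowded.** About 150 events with site as a factor leave little room, and a sparse no-bolus level may overlap with diabetes type. This stands as a condition on the fix. It is not a reason to keep GLP-1 use and omit the rest.

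**Conclusion.** The point holds as a gap in a fixed covariate list. One of three co-treatments that the article treats alike is adjusted for, the other two are not, and diabetes type, arguably the more basic omission, is left to description. Residual confounding of the basal insulin comparison by treatment in use at conception is therefore possible.

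Its size is unknown. The range of 0.15 to 1.8 points rests wholly on assumed prevalences and risk ratios and on zero correlation with the existing covariates, so it should be read as running from negligible to material and not as an estimate. The documents do not support saying that the comparison is confounded or in which direction. The change is worth making because it is cheap and the study is meant to inform the safety of a basal insulin.

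**What to change.** In the primary model and those that copy it:

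- add diabetes type;
- add oral antidiabetic drugs at conception or baseline (yes/no);
- add bolus insulin at conception or baseline (none/human/analogue, with levels merged if sparse);
- define GLP-1 agonist use at conception instead of during pregnancy, and drop it if there are too few users;
- do not adjust for add-on or removal after baseline.

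Tabulate all four by basal insulin group, so that readers can see whether there is any imbalance to adjust for. Confirm that oral drugs in use at conception are on the baseline form, and add the item if they are not.

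The cost is about four extra parameters, one table and possibly one form item. Some precision is lost. With about 150 expected events and many site levels, sparse categories may need merging, or the model may need penalised estimation. No change to patient care is involved.
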